## V. SURGEON SURVEYS

- a. **Pre- and Postoperative Surgeon Surveys** will be administered to assess various factors, such as surgeon change in operative plan, model quality, and utility of the models. The preoperative survey will be administered for intervention cases only. The preoperative survey will be administered after viewing the model but before the operation, and the postoperative survey will be administered after the operation. These surveys are described in Appendix B

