**IV. STUDY DESIGN.**

- a. **Trial Design:** A multi-institution, randomized, single-blind clinical trial
  - b. **Participants and Exclusion Criteria:** Eligible subjects identified from the medical record will be those who are 1) scheduled to undergo RALP surgery, 2) willing to consent to the surgery being performed by one of the surgeons participating in the study, and 3) willing to be assigned by randomization to one of the two groups in the study. Exclusion criteria are 1) prior prostate surgery, ablation, radiation, or androgen deprivation therapy, 2) lack of 3 Tesla or 1.5 Tesla with endorectal coil preoperative MRI imaging, and 3) inability to give informed consent.
  - c. **Randomization:** Each case will be assigned to one of the two preparation methods by a randomization procedure that is stratified by surgeon. Each surgeon-specific randomization schedule will be prepared using permuted blocks of size 2; i.e., each 2-patient block will be some permutation of {VR-aided, Control}. Thus, each surgeon's cases will be randomized in a 1:1 ratio. Use of permuted blocks thus avoids any confounding of preparation method with temporal trends (e.g., trend due to a learning curve.)
- Sequentially numbered opaque sealed envelopes (SNOSEs) will be prepared for each individual surgeon. Each envelope will contain the treatment assignment for one case (intervention or control). There will be an equal number of envelopes containing intervention assignments and control assignments; the total number of envelopes provided to each surgeon will be determined based on the surgeon's historical/anticipated case volume. The treatment code will remain concealed inside the envelope until the moment the case is ready to be prepared.

- d. **Blinding:** Patients, personnel gathering data from the video review, and statistician will be blinded. Control and intervention groups identifiers will be known only to the research personnel opening the sealed envelope for random group assignment and extracting patient data from the electronic medical record.
- e. **Intervention:** For intervention cases, surgeons will be provided with a 3D model to view (a) prior to the operation in addition to the MRI and biopsy results and (b) during the operation in addition to the MRI. For control cases, surgeons will view only the MRI and biopsy results prior to the operation and during the operation itself.

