**Appendix B**  
**Surgeon Pre- and Postoperative Survey**

Preoperative Survey (after viewing MRI but before viewing model)

- 1) Do you plan to perform nerve sparing (none, right, left, bilateral)
- 2) Do you plan to perform bladder neck preservation (yes, no)

Preoperative Survey (after viewing MRI and model)

- 1) Do you plan to perform nerve sparing (none, right, left, bilateral)
- 2) Do you plan to perform bladder neck preservation (yes, no)

Postoperative Survey

- 1) How would you rate your ability to see and define the area of cancer in the MRI (Likert)
- 2) How would you rate your ability to see and understand the relationship between the mass and the adjacent structures in the MRI (Likert)
- 3) How would you rate your ability to see and define the area of cancer in the model (Likert)
- 4) How would you rate your ability to see and understand the relationship between the mass and the adjacent structures in the model (Likert)
- 5) Were there any anatomical structures that you were able to see (or see better) in the model as opposed to the MRI (yes, no)
- 6) If answer to the question above is yes, please explain (free text)
- 7) Were there any structures or details that you could see in the source MRI that were either missing from, or appeared to be inaccurate in the model (yes, no)
- 8) If answer to the question above is yes, please explain (free text)
- 9) Did you modify your preoperative plan in any way as a result of what you saw in the model (yes, no)
- 10) If answer to the question above is yes, please describe how (free text)
- 11) Did you perform nerve sparing (yes, no)
- 12) How much did the model aid you in performing nerve sparing, if performed (Likert)
- 13) Did you perform bladder neck preservation (yes, no)
- 14) How much did the model aid you in performing nerve sparing, if performed (Likert)

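### The operative plan is recorded in the intervention arm only, so plan-to-performed change cannot be compared between arms and the plan cannot be a baseline covariate

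*Combined protocol and SAP*

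**What the plan says.** Section V.a (Surgeon Surveys) gives the purpose of the surveys as assessing factors "such as surgeon change in operative plan, model quality, and utility of the models". It then limits the preoperative part: "The preoperative survey will be administered for intervention cases only". On timing it says: "The preoperative survey will be administered after viewing the model but before the operation".

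Appendix B sets out two preoperative forms. One is headed "Preoperative Survey (after viewing MRI but before viewing model" and the other "Preoperative Survey (after viewing MRI and model" (each heading closes with a bracket). Both contain the same two items: "Do you plan to perform nerve sparing (none, right, left, bilateral" and "Do you plan to perform bladder neck preservation (yes, no". The postoperative survey asks whether each was performed, and whether the plan was modified because of the model.

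Section IV.g makes performed nerve sparing (four categories) and performed bladder neck sparing (yes or no) secondary outcomes in both arms. Section IV.c keeps the assignment concealed "until the moment the case is ready to be prepared". Section IV.d does not list surgeons among those blinded. Section IV.i provides for covariate adjustment only if the randomised groups turn out to differ.

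**The concern.** Change in operative plan is a stated aim of the surveys, yet the plan is written down in one arm only. Three things follow.

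- **No control rate.** Surgeons may depart from an MRI-based plan during the operation for reasons unrelated to a model. Without a control figure, the model's contribution to plan-to-performed change cannot be separated from ordinary intraoperative change.
- **The answer comes after allocation can be known.** The form goes only to intervention cases, so receiving it reveals the arm. A surgeon who expects a model may give a provisional MRI-only answer, which is then easily revised.
- **A baseline variable is lost.** The planned-sparing items use nearly the same categories as two secondary outcomes. A plan recorded before randomisation would be a natural covariate for those outcomes. Recorded in one arm, it cannot be used.

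There is also an asymmetry of procedure: only intervention surgeons commit to a written plan, so any effect of writing one down is bundled with the effect of the model.

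**Working it through.** The plan gives no figure on this point, so the check is mainly a comparison of sections.

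**1. Where is a plan recorded?**

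| Source | Intervention | Control |
|---|---|---|
| MRI-only form (Appendix B) | yes, if Appendix B is followed | no (Section V.a) |
| Post-model form (Appendix B) | yes | not applicable |
| Appendix A covariates | no planned-sparing item | no planned-sparing item |
| Postoperative survey (Appendix B) | asks what was performed | asks what was performed |
| Performed sparing (Section IV.g) | yes | yes |

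Nothing in the documents records a plan for a control case.

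**2. How many cases?** Section IV.h gives 90 patients, 45 per arm. Plans available: about 45 intervention + 0 control = 45 of 90, or 45/90 = 50%, all in one arm.

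**3. Can the plan be a covariate?** Take the model *performed sparing = arm + plan + other covariates*. Dropping cases with no plan leaves only intervention cases, so the arm term cannot be estimated. A missing-plan indicator would equal the control-arm indicator, so the two could not be separated. Imputing control plans from Appendix A covariates would add no observed control information beyond those covariates.

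**4. Do the sections agree on timing?** They do not. Section V.a places the preoperative survey after the model has been viewed; Appendix B also has a form before it.
- If Section V.a is followed literally, no MRI-only plan exists in either arm.
- If Appendix B is followed, an MRI-only plan exists in the intervention arm only.

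The two must be reconciled. Under either reading there is no control plan, so the conclusion does not depend on which prevails.

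**5. What is unaffected?** Performed sparing is collected in both arms and its comparison rests on randomisation, so it needs no baseline plan. Within intervention cases, Appendix B allows the MRI-only plan, the post-model plan and the performed operation to be described in sequence.

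**The case against.** The strongest reply is that no stated analysis breaks. Planned sparing is neither an outcome in Section IV.g nor a covariate in Appendix A. The survey aim can be met within the case, by comparing the two preoperative forms and by asking directly whether the model changed the plan. This stands. It also stands that a control MRI-only form supplies no control rate for change from the MRI-only to the post-model plan, since controls have no second form. What it supplies is a control rate for plan-to-performed change.

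Two stronger readings are tempting and are not supported.

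- A reader might infer that planned and performed sparing cannot be compared at all, or that the change rate says nothing about the model. The limitation is between arms only; the within-arm description survives.
- A reader might put a power gain on the missing covariate. With 45 per arm, d = 0.44 and two-sided alpha 0.05, a two-sample t-test has 54% power. Replacing d by 0.44/√(1 − R²) gives 64% at R² = 0.2 and 76% at R² = 0.4. These figures should not be claimed. Section IV.h ties 0.44 to the primary outcomes, the formula is for continuous data while both sparing outcomes are categorical, and no R² is given in the documents. Appendix A already lists plausible determinants of the plan, such as clinical stage, PIRADS score, tumour location and surgeon, so only the plan's increment over these would count.

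A practical objection also has weight. The model is built after assignment (Section VIII.b), so placing the form before envelope opening brings the surgeon's MRI review forward in every case. Section IV.e says only that controls view the MRI before the operation, not at which step.

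**Conclusion.** The concern holds as a limitation between arms. No operative plan is recorded for any control case, so plan-to-performed change cannot be compared between arms and the plan cannot be a baseline covariate for nerve sparing or bladder neck sparing. Even the intervention-arm MRI-only answer is given when the surgeon can know the allocation. That last step is inferred from who receives the form, not stated in the text.

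In size, the plan is missing for about 45 of 90 cases, which is one whole arm. The consequence is a lost process comparison and a possible but unquantified loss of precision on two secondary outcomes. The randomised comparison of performed sparing is not biased by it. This is a low-severity, inexpensive improvement, but for each case the chance to record a plan before allocation is lost once the envelope is opened. The timing conflict between Section V.a and Appendix B needs correcting in any event.

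**What to change.** 1. Have the surgeon complete the existing two-item MRI-only form from Appendix B in every case, in both arms, before the envelope is opened. Keep the post-model form for intervention cases.
2. Reconcile Section V.a with Appendix B on the timing of the preoperative survey, and revise the restriction to intervention cases to match.
3. State that plan-to-performed change will be compared between arms, using the performed-sparing categories of Section IV.g.
4. Prespecify that the nerve sparing and bladder neck sparing analyses adjust for the recorded plan, instead of adjusting only if imbalance appears as Section IV.i now has it. Add the plan to Appendix A. Claim no power gain.

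**Cost.** Two multiple-choice items in about 45 additional cases (2 × 45 = 90 answers), on a form that already exists. The research coordinator already handles allocation and helps with the surveys (Section VI.b), so no new role is needed. The real demand is scheduling: MRI review and the form must come before envelope opening in all cases, with time left to build the model. A written plan may slightly influence control planning, but the MRI-only form would then act equally in both arms.

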## VI. RESEARCHERS AND RESPONSIBILITIES

- a. **Principal Investigator (PI):** One PI from each participating Site.
  - i. Overall Site point person for study.
  - ii. Coordinates support for study with other Site participants, including Research Coordinator and surgeon users.
  - iii. Primary interface with the Site's IRB.
- b. **Research Coordinator ("RC").** One RC from each participating site. A researcher, fellow, resident or student identified and recruited by the PI. Key activities:
  - i. Identify upcoming cases to be included in the study and assign cases to control group or intervention group using block randomization.
  - ii. Identify, collect and manage:
    1. The MRIs from which the models will be created
    2. Data regarding Control Cases ("**Control Case Data**") and intervention cases ("**Intervention Case Data**")
  - iii. Deidentify each source MRI using deidentifying software (or ensures that Radiology deidentifies the image prior to delivery to the RC); deliver the deidentified image to Ceevra along with a unique identifier.
  - iv. Coordinate with surgeon users to ensure that both the model and the underlying MRI are reviewed prior to intervention cases.
  - v. Assist with administration of the surgeon surveys

- 130           **c. Surgeon Users.** Estimated between one and eight surgeon users (inclusive of  
131           the PI) from each site. Key activities:
- 132               i. Oversee receipt of informed consents from their patients participating in  
133               the study.
  - 134               ii. Provide the mobile phone used for viewing the models
  - 135               iii. Before each intervention case, review the source MRI and then review  
136               the associated model for purposes of case planning.
  - 137               iv. Participate in surgeon surveys.
- 138       **VII. MODEL CREATION KEY PERSONNEL**
- 139           **a. [name], CEO.** Overall Ceevra point person for study.
  - 140           **b. [name], CTO.**
    - 141               i. Oversees the creation of the models from the MRIs.
    - 142               ii. Oversees Ceevra software application and infrastructure.
    - 143               iii. Primary point of contact for user technical support issues.
- 144       **VIII. DATA COLLECTION AND SECURITY PLAN**
- 145           **a. Protocol for Case Data.** Case data will be extracted from the site's EHR system,  
146           and the surveys. It will be tracked via two files:
    - 147               i. The key file will include patient information (listed below) and a unique  
148               identifier. This file will be password protected, maintained solely at the  
149               site, and accessible by site researchers only.
      - 150                   1. Medical Record Number (MRN)
      - 151                   2. Surgeon Number
      - 152                   3. MRI ID #
      - 153                   4. Operation Date
      - 154                   5. Unique Identifier
    - 155               ii. The data file will exist either as a data repository (Open Clinica) or as a  
156               on-site file, per site preference, and will include the unique identifier and  
157               outcomes data, but no PHI. This file will be password protected.
  - 158           **b. Protocol for Model Creation and Data Security**
    - 159               i. PI/RC identifies upcoming intervention cases for which models are to be  
160               created.
    - 161               ii. PI/RC obtains source MRI, deidentifies the same using deidentifying  
162               software (or ensures that radiology deidentifies the image prior to delivery  
163               to the PI/RC), and delivers it to Ceevra along with a unique identifier.
    - 164               iii. Ceevra creates model from the deidentified MRI. Once completed:
      - 165                   1. Delivers the model back to PI/RC, along with the unique identifier.
      - 166                   2. Notifies applicable surgeon user (with copy to PI and RC) that  
167                   model is available for viewing through the mobile app.
    - 168               iv. Prior to the operation, PI/RC contacts applicable surgeon user to ensure  
169               viewing of model along with source MRI.
    - 170               v. The use of the model will be an additional step undertaken by the  
171               surgeons in preparation for surgery and during the operation itself and will  
172               not impact the surgeons' standard review of subject images.
- 173       **IX. TRAINING, MEASURING & COMMUNICATING**
- 174           **a.** Training with surgeon users on accessing/using mobile app and models. Each  
175           surgeon will be trained either in person or via video call. During the training, the

176 surgeon will be trained how to access the models from their mobile phones and  
177 how utilize several viewing features such as showing/hiding anatomical parts;  
178 zooming in/out on the model; and viewing the on the surgical robot.

179 b. Kickoff Meeting (in-person meeting at medical center):

180 i. Introduce participants

181 ii. Outline study processes, timeline and objectives

182 c. Monthly virtual meetings

183 i. Report study results to date

184 ii. Gather feedback – both on specific items and general discussion

185 d. Surgeon Surveys

186 e. Study Conclusion Meeting (in-person): Final study results

187

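### Both arms are to view the MRI before surgery, but only intervention cases have that review prompted, checked and documented, so the model's own effect cannot be fully separated from the prompting

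*Combined protocol and SAP*

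**What the plan says.** Section IV.e defines the contrast. The text for the model arm is: "surgeons will be provided with a 3D model to view (a) prior to the operation in addition to the MRI and biopsy results". The model can also be viewed intraoperatively. The comparator is: "For control cases, surgeons will view only the MRI and biopsy results prior to the operation and during the operation itself". Section VIII.b.v adds that the model is an extra step that will "not impact the surgeons' standard review of subject images". On the design statement alone, the arms differ only in the model.

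The operating sections say more about one arm than the other:

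- VI.b.iv, coordinator: "Coordinate with surgeon users to ensure that both the model and the underlying MRI are reviewed prior to intervention cases".
- VI.c.iii, surgeon: "Before each intervention case, review the source MRI and then review" the model.
- VIII.b.iv, investigator or coordinator: "Prior to the operation, PI/RC contacts applicable surgeon user to ensure" that the model is looked at together with the source MRI. This step belongs to a workflow that opens, at VIII.b.i, with identifying intervention cases.
- V.a, survey: "The preoperative survey will be administered for intervention cases only". Appendix B gives this survey two blocks. The first is completed after the MRI and before the model, and the surgeon states there the nerve-sparing and bladder-neck plan.

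The protocol describes no matching contact, check, listed duty or preoperative survey for control cases.

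**The concern.** The stated objective is to assess whether 3D models improve patient outcomes. If a site follows the text, an intervention surgeon is contacted before the operation, has the MRI review confirmed, and writes down an MRI-based plan before opening the model. A control surgeon is expected to view the MRI, but nobody is assigned to prompt or confirm it.

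This difference arises after allocation. Stratification by surgeon and blocks of 2 balance surgeons and time trends, but they do not balance a procedure that is then applied to one arm. If a prompted, deliberate MRI review affects margins or the nerve-sparing and bladder-neck decisions, part of any observed difference would come from the prompting. Nerve sparing and bladder-neck sparing are themselves the immediate secondary outcomes, and they are the two items that the survey asks the surgeon to commit to.

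**Working it through.** The plan gives no figure on this point, so there is none to reproduce. The check is a comparison of the text by arm, followed by an illustration of size.

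**Step 1: the arms side by side**

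| Element | Intervention | Control |
|---|---|---|
| MRI and biopsy results viewed before the operation (IV.e) | Yes | Yes |
| Coordinator ensures MRI review (VI.b.iv) | Yes | Not described |
| MRI review among the surgeon's listed duties (VI.c.iii) | Yes | Not described |
| Contact before the operation (VIII.b.iv) | Yes | Not described |
| Plan recorded from the MRI alone (V.a, Appendix B) | Yes | No, survey limited to intervention cases |
| 3D model | Yes | No |

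The first row is the same in both arms. The last row is the intended contrast. The four rows between them differ by arm without being part of the intervention as IV.e defines it.

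**Step 2: could the difference be detected or adjusted for?** No covariate in Appendix A records whether, or how, the MRI was reviewed. The postoperative survey asks how well the cancer could be seen on the MRI, but it comes after the operation and does not ask whether or when the MRI was reviewed beforehand. The mixed-model adjustment in IV.i uses the listed covariates, so it cannot address this difference. Surgeons are not among those blinded in IV.d.

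**Step 3: illustrative size.** All inputs here are assumptions, except 45 per arm (IV.h). Let q be the share of control cases that receive an equivalent MRI review without a prompt, and d the effect of that review on the positive-margin rate. Then

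bias = (1 − q) × d.

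| q | d = 10 points | d = 20 points |
|---|---|---|
| 0.9 | 0.1 × 10 = 1 | 0.1 × 20 = 2 |
| 0.7 | 0.3 × 10 = 3 | 0.3 × 20 = 6 |
| 0.5 | 0.5 × 10 = 5 | 0.5 × 20 = 10 |

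Next, assume a 25% control margin rate and no effect of the model. The chance of a significant result is the sum, over all pairs of counts (a, b), of Bin(a; 45, 0.25) × Bin(b; 45, 0.25 − bias) for those pairs where the two-sided p-value is at most 0.05. Section IV.i names both chi-square and Fisher's exact test.

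| Bias (points) | Chi-square | Fisher's exact |
|---|---|---|
| 0 | 5.4% | 2.7% |
| 1 | 5.5% | 2.8% |
| 2 | 6.0% | 3.1% |
| 5 | 9.3% | 5.1% |
| 10 | 23.0% | 14.7% |

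If control surgeons nearly always review the MRI as IV.e says, the effect on error is trivial. It becomes material only if unprompted review is often missing and the review itself matters a good deal.

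**The case against.** The strongest reply is that the control arm is already specified. IV.e says that control surgeons view the MRI and biopsy results, and patients without adequate preoperative MRI are excluded. The lines in VI are short lists of key activities. VIII.b concerns model creation, so it naturally speaks of cases that have a model. The instruction to look at the MRI first can be read as a safeguard against the model replacing the MRI, which agrees with VIII.b.v. Some contact is also unavoidable, because the surgeon has to be told that a model exists (VIII.b.iii). The same surgeons treat both arms.

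Most of this stands. A reader might infer that MRI review is required only in the intervention arm. IV.e rules that out: review is specified for both arms, and the arms differ in prompting, checking and documentation. A reader might also infer that no benefit could be credited to the model. That goes too far, because the randomised comparison validly estimates the effect of the model as delivered, and the documents do not show that the prompting has any effect.

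The reply does not close the gap. VI.b.iv names the MRI as well as the model, so it is more than a notice that a model is ready. The survey block completed before the model concerns the MRI alone. A design statement that nobody is assigned to carry out is not equivalent to a check, a listed duty and a recorded plan.

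**Conclusion.** The point holds as a moderate one. The text supports an asymmetry in the prompting, verification and documentation of MRI review, and none in whether the MRI is to be viewed. The trial can answer whether the package (model, contact and MRI-based plan survey) does better than unprompted MRI review. It cannot fully isolate the contribution of the model, and the data to be collected would not show how much the prompting mattered.

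The size is unknown. The documents give no rate of MRI review by arm, no effect of such a review and no margin rate for this calculation. The 1 to 10 point biases and the error rates above are illustrations of those assumptions, and the upper figures need both a low review rate in control cases and a large effect of review. The lower end, 1 to 2 points, is negligible. The case for acting is that the asymmetry is avoidable at little cost and cannot be measured afterwards as the plan stands.

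**What to change.** 1. Reword VI.b.iv, VI.c.iii and VIII.b.iv to cover every study case. The coordinator makes the same contact, at the same interval before the operation, to confirm review of the MRI and biopsy report. In intervention cases only, the model is then viewed.
2. Change V.a and Appendix B so that the two plan questions following MRI review are asked in both arms, and the block following the model in intervention cases only. V.a now places the preoperative survey after the model has been viewed, while Appendix B also has a block before it, so the same edit should reconcile the two.
3. Add a yes/no item, in both arms, for completion of the MRI review before the operation.
4. If the sponsor prefers to leave the procedures as they are, IV.e and the objective should define the intervention as the package, and the results should be worded accordingly.

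The cost of the first three changes is protocol wording, about 45 additional reminders and two-item surveys (one per control case) by the existing coordinators, and one data field. Control preparation becomes slightly more structured than unprompted routine care, although it only enforces what IV.e already states. Surgeons will still know the allocation, so equal contact removes this source of difference and not every possible difference in effort.

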- f. **3D Model Creation and Delivery:** MRI scans will be deidentified and sent in Digital Imaging and Communications in Medicine (DICOM) format to Ceevra, Inc., where a patient-specific 3D model for each intervention patient will be created. The Prostate Imaging-Reporting and Data System (PIRADS) score will be used to identify and label prostate lesions. In addition, the biopsy report, will be used to create a patient-specific pathology map that will be included in the model to assist the surgeon in understanding the location of biopsy-proven cancer within the prostate. Models will be delivered to a mobile application on the surgeon's smartphone (Ceevra Reveal) and viewed as described above. In addition, the surgeon may view the model picture-in-picture on the robotic console screen using a video cable connection between the surgeon's smartphone and the surgical robot.
- g. **Outcomes Measures and Covariates:** The primary outcome measure is oncologic outcomes after RALP. This outcome will be measured at three time points: immediately postoperative, short term, and a final assessment when oncologic and functional outcomes have reached a steady state. Oncologic outcomes will be measured as margin status (positive or negative), PSA (linear and detectable/undetectable) at the initial assessment (which in most cases is three months postoperatively but may occur any time between 3 and 6 months), and PSA ( $>0.1$ ) at the final assessment (to be collected after 18 months but no later than 24 months). Additionally, any use of androgen deprivation therapy or radiation therapy will be captured at 24 months as an adverse oncologic outcome.
- Secondary outcomes are the urinary and sexual function of the patient, measured at the same three time points as above. For urinary function, this is bladder neck sparing (yes or no), measured immediately postoperatively, and incontinence pads per day, measured at both 3-6 months and 18-24 months postoperatively. For sexual function, this is nerve sparing (none, left, right, or bilateral), measured immediately postoperatively, followed by SHIM score, measured at both 3-6 months and 18-24 months postoperatively.
- Demographic data, disease-specific, surgery-specific, and surgeon-specific covariates will be collected from the medical record as well, see Appendix A.

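### The surgeon's pre-model operative plan is not protected: section V times the preoperative survey after the model, and VIII.b lets the surgeon know the model is viewable before any survey answer is due

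*Combined protocol and SAP*

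**What the plan says.** Appendix B contains two preoperative questionnaires with the same two items, on planned nerve sparing and planned bladder neck preservation. The first is headed "Preoperative Survey (after viewing MRI but before viewing model"; the second follows viewing of both MRI and model. Section V names change in operative plan among the aims of the surveys and limits the preoperative survey to intervention cases. It describes a single preoperative administration, placed between viewing the model and the operation, and refers to Appendix B for the content.

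On delivery, section IV.f states: "Models will be delivered to a mobile application on the surgeon's smartphone (Ceevra Reveal) and viewed as described above". Section VIII.b.iii lists two vendor actions once a model is complete. The first is "Delivers the model back to PI/RC, along with the unique identifier". In the second, the vendor "Notifies applicable surgeon user (with copy to PI and RC) that" the "model is available for viewing through the mobile app". Item iv then adds: "Prior to the operation, PI/RC contacts applicable surgeon user to ensure" that the model is viewed together with the source MRI.

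Section VI.c.iii requires the surgeon to look at the MRI first and the model second. Section VI.b gives the research coordinator a supporting role in the surveys.

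**The concern.** The two Appendix B questionnaires form a before-and-after pair, and their difference is the only prospective measure of whether the model changed the plan. The pair works only if the first answer is given by a surgeon who has not yet seen the model. Once the model has been seen, that answer cannot be recovered.

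The operational sections do not secure this order. The surgeon learns directly from the vendor that the model is ready, on the surgeon's own phone, and no section makes viewing wait for the first questionnaire. A site that followed section V literally would give the preoperative survey only after the model. At stake is a stated survey aim: the plan could report that the model seldom changes surgical planning when the baseline had simply been recorded too late. With no time stamps specified, the affected cases could not be identified afterwards.

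**Working it through.** The plan gives no figure on this point, so the main check is to set the sections side by side and follow one intervention case.

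1. **Required order (Appendix B):** MRI, first questionnaire, model, second questionnaire, operation.
2. **Order in section V:** model, preoperative survey, operation. No administration before the model is mentioned. This conflicts with step 1.
3. **Order in section VI.c.iii:** MRI, then model. The sequence agrees with Appendix B, but no survey stands between the two.
4. **Order in section VIII.b:** model complete; delivery to the PI or coordinator; notice to the surgeon, with the model already viewable; later contact from the PI or coordinator. That contact is there to make sure viewing takes place. It does not check whether the first questionnaire has been answered.
5. **Conclusion from 1 to 4:** only the heading of the first questionnaire protects the pre-model answer. Every operational section either omits the step or, in section V, puts the survey after the model.

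**Direction of the bias.** A surgeon who has already seen the model will tend to give the post-model plan as the before answer. The two answers then agree more often than they should, and observed change is too low.

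**Illustration of size.** Only the 45 intervention cases come from the documents (section IV.h: 90 patients, 45 per arm). The true change rate and the share of early openings are assumptions.

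- Let p be the true share of cases in which the model changes the plan, and e the share in which it is opened before the first questionnaire. If early opening removes all observable change in a case, observed change = p × (1 − e).
- Assume p = 0.30: 0.30 × 45 = 13.5 cases.
- e = 0.25: 0.30 × 0.75 = 0.225, and 0.225 × 45 = 10.1 cases.
- e = 0.50: 0.30 × 0.50 = 0.15, and 0.15 × 45 = 6.75 cases.

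This is the largest dilution at each value of e. If surgeons who opened early could still report their MRI-only plan accurately, observed change would stay at 30%. The range is therefore 22.5% to 30% for e = 0.25 and 15% to 30% for e = 0.50. The documents give no value for p or e.

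**The case against.** The strongest reply has four parts.

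- **Appendix B already states the order.** Section V refers to it, the coordinator helps with the surveys, and VIII.b concerns model creation and data security, where silence on surveys is unsurprising. This is fair as far as it goes: a careful site could collect the answers correctly. It does not remove the conflict with section V, and it leaves the order to each site's habits.
- **Change of plan is measured a second way.** Postoperative items 9 and 10 ask directly whether and how the model altered the plan, and do not depend on the first questionnaire. This stands, but they are self-report after surgery and do not replace a plan recorded beforehand.
- **The surveys are peripheral.** They are not among the primary or secondary outcomes in section IV.g, and section IV.i specifies no survey analysis. This stands and limits the weight of the point.
- **A hold on the model could harm the trial.** If a missed survey kept the model from the surgeon, the randomized intervention would not be delivered, for the sake of a descriptive measure. This also stands, and any fix needs a fallback.

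A reader might also infer that surgeons can open a model before the site has matched it to the patient, and so plan from another patient's anatomy. The documents do not support that. They describe no matching step that could be bypassed, and do not say how a model is labelled in the app. The PI or coordinator receives the model with its identifier and is copied on the notice. The key file is described as "site, and accessible by site researchers only", but surgeons are listed in the researchers section, so the documents do not show that they lack the link. The surgeon must also view the source MRI alongside the model. The most that can be said is that no identifier check before release is specified.

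**Conclusion.** The concern holds for the survey. Sections V, VI.c.iii and VIII.b do not secure the pre-model answer that Appendix B requires, and section V contradicts it on timing. As written, the workflow allows the before answers to contain the model's effect, with bias toward no change in the paired measure. That direction assumes that an early look pulls the first answer toward the post-model plan. The size is unknown, and the figures above are upper limits on dilution under assumed rates.

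The reach is limited. It would be wrong to infer that the primary result is at risk: the randomized comparison, the sample size and the primary analysis do not use these answers. This is a cheap improvement to a stated survey aim. The missing identifier check is a side note, and no claim about patient safety follows from it.

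**What to change.** 1. Reconcile section V with Appendix B, so that both describe two preoperative administrations, before and after the model, for intervention cases.
2. Change VIII.b.iii.2 so that the vendor's notice goes to the PI or research coordinator first. That person collects the two pre-model answers with a time stamp, then passes the notice to the surgeon and records the time.
3. State a fallback: if the first questionnaire is missed, the model is still released before surgery, so the randomized intervention is never withheld.
4. State that a case enters the paired change-of-plan analysis only if the pre-model answers precede the notice, and report how many cases are left out. Show items 9 and 10 beside it as a separate retrospective measure.

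The cost is a wording change in two sections, a two-question coordinator step in about 45 cases and a slight delay in access to the model. Steps 2 and 3 redirect a message and need no new app function. The notice is only a proxy for opening: the documents do not say whether a model can be seen in the app before the surgeon is told of it, so this should be confirmed with the vendor. The same edit could state whether the identifier is checked against the key file before the notice is passed on.
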